### Interventions

#### EMDR

The EMDR intervention will follow the Dutch translation of the EMDR protocol for children, consisting of the eight-phase protocol of Shapiro [36] (updated Dutch protocol [32, 37]). The phases are history taking, treatment planning, preparation, reprocessing, installation of a positive cognition, check for and processing any residual disturbing body sensations, positive closure, and evaluation. At the start of the first session, the child and caregiver(s) are present. This session consists of psychoeducation on PTSD and the rationale for trauma treatment, and the specifics of EMDR are explained shortly. Next, an inventory of possible target memories is made. From there on, up to seven sessions of EMDR are being offered aiming at the reduction of emotional disturbance associated with the most distressing traumatic memories and/or fear of images of what could have happened. The therapist starts with the target memory with the highest Subjective Unit of Distress (SUD) on a 1–10 scale. Standard eye movements are applied for bilateral stimulation, although alternative distractive tasks can be chosen as well. The intervention consists of up to eight weekly sessions of 75 min. Criteria for early termination are when all the memories listed on the case conceptualization do not evoke tension and/or the complaints have disappeared.

#### KIDNET

For KIDNET, a Dutch translation of the NET protocol adapted for children is followed [28, 38]. The therapist starts the first session with the child and caregiver(s). Psychoeducation on PTSD complaints and the indication for Narrative Exposure Therapy will be given to both the caregiver(s) and child. Furthermore, the specifics of KIDNET will be explained shortly. The therapist will then continue the session with the construction of the lifeline. A rope or a string will be placed on the floor/table representing the course of life of the child starting from birth. The other end of the rope/string is rolled up to indicate the future. Next, the child can lay stones and flowers on the lifeline in a chronological way representing fearful, shocking, and/or traumatic events (stones) and pleasant and meaningful moments (flowers), respectively. The lifeline always starts with a flower representing birth. In this session, the child will describe all the flowers and stones briefly and factually. The next sessions are devoted to following the lifeline chronologically, processing the traumatic events per session (and in some sessions also the pleasurable and meaningful events) through narrative exposure. Each session the therapist will write down the narrative belonging to the period discussed in that session (stone and/or flower). The therapist reads the narrative to the child in the subsequent session and asks the child if he or she wants to change anything. After the rereading, the narration is continued chronologically along the lifeline. The last session the therapist will read the complete narration to the child and will hand it as a document to the child. The intervention consists of up to 8 weekly sessions of 75 min. Criteria for early termination are when all the memories listed on the case conceptualization do not evoke tension and/or the complaints have disappeared.

#### Waitlist control group

The aim of the current trial is to evaluate the effectiveness of KIDNET and EMDR treatment. Therefore a waitlist control group is chosen as a comparator. Once trauma-focused treatment has been indicated, a child may be assigned to the waitlist control group. When a participant is randomized to the waitlist control group, he or she will receive no trauma treatment for 8 weeks. This implies there will be no contact (except in case of emergency) for 8 weeks before the post waitlist measurements (T2) and then the start of either one of the treatment conditions (second randomization).

#### Parental guidance

During the intervention period (both EMDR and KIDNET) caregivers will receive parental guidance of one to four sessions of one hour, one at the beginning, two during treatment, and one at the end. Parental sessions are aimed to support the child during their trauma-focused intervention. The sessions focus on how to deal with the symptoms of the child, how to support the child, and how to be emotionally available as a parent with respect for the child’s own space and time to process. The sessions with caregivers have a maximum duration of 75 min each. The sessions (in terms of duration, kind, and frequency) that caregivers receive will be registered.

#### Modifications and concomitant care

There are no planned intervention modifications and no planned circumstances whereby participants will be removed from the intervention by the trial investigators. Participants may withdraw from the study and intervention at any time. Trauma-focused treatment, other than the assigned condition, is not allowed during the study period. Other usual care for participants continues throughout the trial and will be monitored.

#### Treatment integrity and adherence

All sessions will be video- or, if the participant only consents with audio, audio-taped. Treatment fidelity will be checked by assessing videotaped (or audiotaping) sessions. Although it is expected that children will be able to communicate in the Dutch language, interpreters will be used when this is needed (e.g., for communication with caregivers). All therapists follow supervision sessions (once every 6 weeks), using video recordings of the sessions, from an accredited KIDNET supervisor and EMDR supervisor ([name]) for the duration of the study to optimize treatment adherence. If the therapist estimates that a limited number of extra sessions are needed to complete the trauma treatment, this can be decided during the supervision with the supervisor’s approval and will be noted.

#### Post-trial care

If a participant has residual complaints or another request for help during the last follow-up measure it will be discussed in our multidisciplinary team. In case of residual PTSD complaints, it will be discussed if the participant can receive additional trauma-focused treatment at ARQ Center’45 or a suitable referral to treatment nearby the living location of the participant will be made in co-operation with the referrer of the participant. The intervention is not expected to cause any harm.

### Measures

#### Timing of measurements

The Life Events Checklist-5 (LEC-5) will solely be administered at T1. The assessor will note important changes or events during the first and last measurement at the last measurement (T3 or T4). The *Clinician-Administered PTSD Scale for Children and Adolescents* (CAPS-CA-5 [39, 40]), the Children’s Revised Impact of Event Scale (CRIES-13 [41, 42]) parent and child version, the Strengths and Difficulties Questionnaire (SDQ [43]) parent and child version and the KIDSCREEN-27 [44] will be administered at each timepoint. Lastly, the CRIES-13 child version will be administered at each session by the therapist during the intervention.

#### Primary outcomes

##### Posttraumatic stress disorder and symptoms

At baseline, the LEC-5 will be administered to register the number and type of traumatic events the child was exposed to. To assess the presence of a (partial) PTSD diagnosis and symptom severity the CAPS-CA-5 for DSM5 will be administered. The CAPS-CA-5 is a 30-item structured clinical interview assessing PTSD symptoms based upon DSM5 criteria for children and adolescents aged seven and above. Symptoms in relation to the past month are examined. Symptom severity ratings are based on symptom frequency and intensity, with a severity score of two or higher indicating the presence of a symptom. CAPS-CA-5 can be administered reliably by different interviewers, with a kappa coefficient of .75 for the Dutch (DSM-IV) version [45] and .80 for the English DSM5 version [46]. The Dutch CAPS-5 is a carefully translated instrument with adequate psychometric properties [47].

Furthermore, both the child version and the parent version of the CRIES-13 will be administered. The CRIES-13 is a brief self-report measure to screen children aged 8 years and above for the severity of PTSD symptoms. The CRIES-13 consists of 13 items to assess intrusion, avoidance, and hyperarousal. The CRIES-13 child version has demonstrated good reliability among war-affected children and adolescents [42]. A study evaluating the reliability and validity of the CRIES-13 child version in a large clinically referred sample in the Netherlands (*n*=395) reported an internal consistency using Cronbach’s *α* of .89 and a test-retest reliability coefficient of .85 [48].

#### Secondary outcomes

##### Behavioral and emotional symptoms

The SDQ is a brief behavioral screening questionnaire that measures emotional symptoms, behavioral problems, hyperactivity, peer relation problems, and prosocial behavior. Both child and caregiver versions are administered.

##### Quality of life

The KIDSCREEN-27 (child version) is a generic quality of life measure based on physical well-being, mental well-being, autonomy, relationship with parents, friendships, and functioning at school. The KIDSCREEN-27 has been designed and normed for children and adolescents aged 8–18 years.

##### Demographic variables

A social demographic form will be filled in by the assessor based on the intake interview to obtain information on age, gender, country of birth, asylum status, time in the Netherlands, and whether the child and/or parents need(s) a translator.

##### Important changes or events between Time 1 and Time 3/Time 4

A form with several questions about important events or changes during the first and last measurement will be filled in by the assessor. Examples are changes in asylum status, change of location within the Netherlands, and changes in the family situation (divorce or reunification).

#### Translation of instruments

All self-report questionnaires, except the KIDSCREEN-27, for which no validated translations were available, have been translated—and subsequently back-translated by professional bi-lingual interpreters. Because they are spoken by relatively large numbers of refugees in the Netherlands, Tigrinya and Arabic have been chosen for translation. The assessments of participants, speaking a language other than Tigrinya or Arabic and when an officially back-translated questionnaire is not available in their language, will be done in Dutch and translated on the spot by a telephone interpreter.

#### Sample size

Previous studies with refugee children show large between-group effect sizes for PTSD symptom severity for KIDNET vs control group and EMDR vs control group [18, 20, 21, 25]. Therefore, at least a medium effect size can be expected when comparing the two treatment conditions (EMDR and KIDNET) to the waitlist control group. With the following assumptions: a correlation between assessments of 0.40, a modest effect size of intervention (ES *f*=0.20), a power of .80, alpha of .05, and two groups (EMDR, KIDNET versus waitlist control group), a total sample of 78 participants will be needed (26 participants per condition), (G*power [49]).

We hypothesized that both interventions (EMDR and KIDNET) are effective in reducing post-traumatic stress symptoms. In case there is a small difference in effectiveness, we aim to detect it. Therefore, the number of participants needed to detect a small effect size (*f*=0.17) is computed, resulting in a preferable sample size of 78 participants (39 participants per treatment condition; EMDR and KIDNET).

After the waitlist period of 8 weeks, the second randomization will take place. Participants will be randomly assigned to EMDR or KIDNET which results in 13 extra participants in both treatments group and thereby a total of 39 participants in both treatment groups. Since a crossover design is not used, the data of the participants (*n*=26) who were secondly randomized into a treatment condition will only be used in the analyses of EMDR versus KIDNET. A conservative 20% attrition rate will be taken into account, resulting in a total required sample of 93 participants.

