Peltonen et al. (2019) [20]	Refugee children and children with experiences of family violence aged 9–17 living in Finland	50	RCT	KIDNET vs TAU	7–10 sessions of 90 min	CRIES-13	pre-, mid-, and posttreatment and 3-month follow-up	No evidence was found for superior effects of NET versus TAU on reduction in PTSD symptoms. There was a decrease in PTSD symptoms regardless of treatment condition; however, this decrease was significant in the NET group only. The effect sizes (Cohen’s *d*) were large in NET (0.83), but small in TAU (0.37)
Ruf et al. (2010) [21]	Refugee children aged 7–16 in Germany	26	RCT	KIDNET vs waitlist	7–8 sessions of 90–120 min	UPID	Pretreatment, 4-weeks, 6-month, and 12-month follow-up	The KIDNET-group (ES=1.9), but not the waitlist (ES=0.3), showed clinically relevant and significant reduction in PTSD symptoms.
Said et al. (2020) [22]	UCM aged 16–17 from Sudan, Vietnam, and Albania in the UK	4	Pre-post study	KIDNET	9–20 sessions	CRIES-8 + CPSS-5	pre-, start-, mid-, and posttreatment	PTSD symptoms were below the clinical range after treatment. All three participants who completed KIDNET met the criteria for reliable improvement.
Schauer et al. (2004) [23]	Refugee child aged 13 from Somalia in Uganda	1	Case study	KID-NET	4 sessions of 60–90 min	PDS	Pretreatment and at 6-month follow-up	The post-test showed that the symptoms decreased to a degree below the diagnostic threshold for PTSD.

Note: *UPID* UCLA PTSD index for DSM-IV, *CIDI* Composite International Diagnostic Interview, *PDS* The Posttraumatic Diagnostic Scale, *HSCL* the Hopkins Symptom Checklist-25, *CRIES* Child Revised Impact of Events Scale, *CPSS-5* Child PTSD Symptom Scale

**Table 2 Tab2:** Studies on Effectivity of EMDR With Refugee Children

Study	Studied population	N	Study design	Treatment	Number and duration of sessions	Instrument PTSD	Measure points	Results
Oras et al. (2004) [24]	Refugee children aged 8–16 in Sweden	13	Pre-post study	Age 8–13: EMDR + play therapy Age 13+: EMDR + conversational therapy	Total 5–25 sessions of which 1–6 sessions of EMDR	PTSS-C, GAF	Pre- and posttreatment	A significant improvement was found in the functioning level and all PTSS-C scales. The improvement in the functioning level was significantly correlated with the reduction of the PTSD-non-related and the depression symptoms, but not with the PTSD-related symptoms.

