### Statistical analyses

Descriptive statistics and analysis of variance will be performed. All three groups will be compared with regard to pre-treatment variables such as demographic variables (age, gender, ethnicity). To test the effectiveness of EMDR vs waitlist control group and KIDNET vs waitlist control group, analyses of variance will be performed with time (T1 and T2) as within-subject variable, and treatment (EMDR, KIDNET, or waitlist control group) as between-subject variable. To test the effectiveness of EMDR compared to KIDNET, analyses of variance will be performed with time (pre-treatment, post-treatment, and follow-up) as within-subject variable, and treatment (EMDR and KIDNET) as between-subject variable. Both analyses will be done twice; with per-protocol sets and intention-to-treat sets. SPSS will be used for multiple imputations techniques for missing data, the per-protocol analyses, and the intention-to-treat analyses. CONSORT criteria will be followed for the statistical analyses (and reporting) of randomized controlled trials. Repeated measures (per session) will be conducted to evaluate treatment progress (CRIES-13 child version).

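### The sample of 78 is described as a two-group calculation but matches a three-group interaction test, so each therapy-versus-waitlist comparison at 26 v 26 has about 73% to 78% power, not 80%

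*Protocol article*

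**What the plan says.** The Sample size section of the protocol article assumes "a correlation between assessments of 0.40, a modest effect size of intervention (ES *f*=0.20), a power of .80, alpha of .05". It continues "and two groups (EMDR, KIDNET versus waitlist control group), a total sample of 78 participants will be needed (26 participants per condition"), so the calculation is described as one for two groups and arrives at 78 participants, 26 in each of three conditions. Waitlist children who are randomized a second time are kept for the EMDR-KIDNET comparison only, so they add nothing to the comparisons with waitlist.

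The Statistical analyses section gives the aim of the first analysis as "To test the effectiveness of EMDR vs waitlist control group and KIDNET vs waitlist control group". The model it names has time at T1 and T2 and a treatment factor with three levels. Research questions 1 and 2, under Objectives of the current trial, are likewise separate: one for EMDR against waitlist, one for KIDNET against waitlist.

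The effect size is supported by the sentence "Previous studies with refugee children show large between-group effect sizes for PTSD symptom severity", citing references 18, 20, 21 and 25. For reference 20, the Finnish trial of KIDNET against treatment as usual, Table 1 says "No evidence was found for superior effects of NET versus TAU on reduction in PTSD symptoms".

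**The concern.** The section gives every input a reader needs to check the number, and the number does not follow from them. If 78 comes from a different test than the one described, the 80% power belongs to that other test. A three-group interaction on 2 degrees of freedom asks whether the three arms change differently. A significant result does not say which therapy beats waitlist, which is what hypotheses 1 and 2 ask.

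The label matters too. A reader told that 80% power covers a modest effect may take f = 0.20 for a small difference between arms. In the version of f that reproduces 78, it is a difference in change of at least 0.80 SD. The evidence offered for expecting large effects also includes one trial that, by the article's own table, found no between-group advantage.

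**Working it through.** **Inputs.** From Sample size: f = 0.20, correlation ρ = 0.40, alpha = 0.05, power = 0.80, stated total 78 (26 per condition). From Statistical analyses: m = 2 time points (T1, T2) and three treatment levels. No division of alpha is stated.

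**Formula.** For the group-by-time interaction in repeated-measures ANOVA, as G*Power computes it: λ = f²·N·m/(1 − ρ), with df1 = (k − 1)(m − 1) and df2 = (N − k)(m − 1). Power is the upper tail of the noncentral F beyond the alpha = 0.05 critical value.

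**Step 1: the plan's figure as described (k = 2).**
- N = 62: λ = 0.04 × 62 × 2/0.60 = 8.27, df 1 and 60, power 80.8%. N = 60 gives 79.4%, so 62 is the smallest total with equal groups.
- N = 78: λ = 10.40, df 1 and 76, power 89%.

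The stated 78 is not reproduced.

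**Step 2: three groups (k = 3).**
- N = 76: λ = 10.13, power 80.4%. Rounded up to equal arms, this is 78.
- N = 78: λ = 10.40, df 2 and 75, power 81.5%.

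This reproduces 78. Other combinations were tried: two or three groups; two, three or four time points; interaction, between and within effects. At the stated inputs no other one gives 78.

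**Step 3: what f = 0.20 means in SD units.** For two equal groups, a difference in change D (in units of the SD at one time point) gives λ = D²·N/[8(1 − ρ)]. Setting this equal to 2f²N/(1 − ρ) gives D = 4f = 0.80. For three equal groups with changes (D, D, 0), λ = D²·N/[9(1 − ρ)], so D = f·√18 = 0.849. As a pairwise f that is 0.849/4 = 0.212.

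**Step 4: power of one therapy-versus-waitlist contrast, 26 v 26 (N = 52, df 1 and 50).**

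| Reading of f = 0.20 | D (SD) | λ | Power |
|---|---|---|---|
| Pairwise effect | 0.80 | 6.93 | 73.3% |
| Three-group effect, therapies equal | 0.849 | 7.80 | 78.2% |

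Using the pooled three-arm error (75 df) changes these only to 73.9% and 78.7%.

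**Step 5: effect of attrition.** With 31 per arm enrolled and 20% lost, 24.8 per arm remain, and the two figures become 71% and 76%. If all 31 were evaluable they would be 80.8% and 85.1%.

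**Step 6: same 26 v 26, with T2 analysed adjusted for T1.** The change score has SD √[2(1 − 0.40)] = 1.095. The residual SD after adjustment is √(1 − 0.40²) = 0.917. The noncentrality (D/SD)·√(26/2) is 0.80/0.917 × 3.606 = 3.15 at 0.80 SD and 3.34 at 0.849 SD. With 49 df, power is 87.0% and 90.5%.

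**Step 7: the cited evidence.** For the Finnish trial, the 0.83 and 0.37 in Table 1 are effects within each arm, and the same entry reports no superiority. The 1.9 and 0.3 given for the German waitlist trial (reference 21) are also per-arm figures, although the gap between them is large.

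**The case against.** The strongest reply is that little turns on this. If 78 is the three-group number and the therapies are equally effective, as the article hypothesizes, pairwise power is 78.2%, within two points of the target. The 73% figure needs f = 0.20 to be the pairwise effect. The article also expects at least a medium effect and plans below it. At f = 0.25, assumed here as the conventional medium value, 26 v 26 gives about 90%. The other cited results in Table 1 point to large effects even without the Finnish trial. All of this stands, and it limits how serious the point is. It does not make the group count right or move the 80% onto the pairwise tests.

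A second reply is that the Statistical analyses section already states the pairwise purpose and never makes the overall interaction decisive, and that contrast details may be in an analysis plan not shown. That also stands. A reader might infer that the trial intends to answer hypotheses 1 and 2 with the overall test alone, and the article does not say so.

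Could another input rescue the two-group wording? A correlation of 0.50 would give 52 for two groups, exactly 26 per arm, but the article states 0.40. Three time points would give 50, but this comparison uses T1 and T2 only. Both therapies combined against waitlist (52 v 26) at 0.80 SD has λ = 0.64 × (52 × 26/78)/1.20 = 9.24 and power 85%. That does not yield 78 as the required total either, and it tests neither hypothesis.

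**Conclusion.** The point holds at moderate weight. At the stated inputs two groups need 62, and 78 belongs to the three-group by two-time interaction. Each of the two comparisons that answer hypotheses 1 and 2 has about 73% power (f = 0.20 pairwise) or about 78% (f = 0.20 across three groups, therapies equal), so the stated 80% is missed by 2 to 7 points. This rests on ρ = 0.40, two-sided alpha 0.05 per contrast, equal variances at T1 and T2, and 26 evaluable per arm. The reference to large between-group effects is contradicted by Table 1 for the Finnish trial.

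A reader might go further and infer a severe lack of power. The documents do not support that:
- Power of 35% for the weaker therapy arises only if it has half the effect of the other, whereas the article expects no large difference.
- Power of 25% arises only if f = 0.20 is read as d = 0.40, which the article does not say and which the reproduction of 78 rules out.
- Power of 63% to 69% arises only with a Bonferroni split that the article does not state.

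These are sensitivity assumptions and not properties of the plan. The correction should be made, but the design does not depend on it.

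**What to change.** In Sample size:
- State that 78 is the number for the three-group by two-time interaction (power 81.5%), and remove the description as two groups.
- Add the power of each 26 v 26 contrast with the planned ANOVA: 73% to 78%, with the reading of f behind each end.
- Replace the word modest with the detectable difference in change, about 0.80 to 0.85 SD.
- Reword the sentence on earlier trials so that it does not rely on reference 20, and say where the Table 1 figures are per-arm effects.

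In Statistical analyses, name the EMDR-waitlist and KIDNET-waitlist contrasts as the tests of hypotheses 1 and 2.

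Optionally, analyse T2 adjusted for T1 (ANCOVA). This is a choice of analysis and not a correction of the error, but on the same 26 v 26 it gives about 87% to 90% power for 0.80 to 0.85 SD.

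The cost is some rewording and a less favourable stated power. No extra participants are needed. The article says analysis waits for the final assessment, so the change can be made and dated before any results are seen.

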### Objectives of the current trial

The aim of the current study is to investigate the efficacy of both EMDR and KIDNET compared to a waitlist control group. The research questions are:
Is EMDR effective in decreasing PTSD and posttraumatic stress symptoms, decreasing behavioral and emotional symptoms, and improving quality of life in refugee children and adolescents, compared to a waitlist control group?

We hypothesize that EMDR is more effective in reducing PTSD and posttraumatic stress symptoms, behavioral and emotional symptoms, and improving quality of life in refugee children and adolescents, compared to a waitlist control group.
2)Is KIDNET effective in decreasing PTSD and posttraumatic stress symptoms, decreasing behavioral and emotional symptoms, and improving quality of life in refugee children and adolescents compared to a waitlist control group?

We hypothesize that KIDNET is more effective in reducing PTSD and posttraumatic stress symptoms, behavioral and emotional symptoms, and improving quality of life in refugee children and adolescents, compared to a waitlist control group.
3)Is there a difference in effectivity between EMDR and KIDNET?

We hypothesize that both interventions (EMDR and KIDNET) are effective in reducing post-traumatic stress symptoms. Therefore, we do not expect (large) differences in effectiveness between the two interventions and hypothesize that both interventions equally reach efficacy in refugee children aged 8–18 years. However, this comparison has not been done before, in case there is a small difference in effectiveness, we aim to detect it.

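### The plan claims sensitivity to a small EMDR–KIDNET difference, but its f=0.17 is about 0.7 SD in the planned analysis, and the equal-efficacy hypothesis has no test that could confirm it

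*Protocol article*

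**What the plan says.** The Sample size section gives two calculations. The first, for the waitlist comparison, assumes "a correlation between assessments of 0.40", together with f=0.20 (which it calls modest), 80% power and α=0.05, and arrives at 78 children. The second concerns the two therapies. It opens with the aim "In case there is a small difference in effectiveness, we aim to detect it". The effect that it enters is f=0.17, which it labels small. The outcome per therapy is given as "39 participants per treatment condition; EMDR and KIDNET", that is, 78 in all, a size described as preferable. The 39 are made up of 26 children first randomized to each therapy and 13 added from the waitlist group by the second randomization.

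The Statistical analyses section tests EMDR against KIDNET by analysis of variance, with time (pre-treatment, post-treatment, follow-up) as the within-subject factor and treatment as the between-subject factor. It states no equivalence margin and no confidence-interval criterion.

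Under research question 3, the Objectives section says that no (large) difference is expected. The authors "hypothesize that both interventions equally reach efficacy in refugee children", and the section repeats the aim of detecting a small difference should one exist.

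**The concern.** Cohen's f for a within-between interaction is not on the scale on which readers judge a difference between two treatments. It is divided across both groups and all time points, so an f that looks small can stand for a substantial difference in change. If f=0.17 is really about 0.7 SD, the article promises a sensitivity that the trial does not have.

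Hypothesis 3 adds to this. The plan expects equality, says that it could see a small departure from it, and then names only a test of difference. This is the first head-to-head comparison of the two therapies in this population. A non-significant result published beside a claim of sensitivity to small differences would invite more confidence in equality than the data could give.

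**Working it through.** **Inputs.** From Sample size: f=0.17, N=78 (39 per therapy), correlation ρ=0.40, power 0.80, α=0.05. The last three are stated for the waitlist calculation only; that they carry over is an assumption. From Statistical analyses: k=2 groups and m=3 times for EMDR versus KIDNET.

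**Formula.** For the within-between interaction in the G*Power convention, λ = f²·N·m/(1−ρ), with df₁=(k−1)(m−1), df₂=(N−k)(m−1) and a noncentral F distribution; sphericity is assumed.

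**Step 1: the plan's own figures.**
- Waitlist: f=0.20, ρ=0.40, three groups and two times give N=76, or 78 when rounded up to equal groups of 26. This matches the stated total (although the text says two groups) and supports this choice of formula.
- EMDR versus KIDNET, three times: λ = 0.17²×78×3/0.60 = 11.27 on 2 and 152 df, power 85%. With 74 children (93×0.8=74.4), power is 83%. Under the planned analysis, 78 is enough for f=0.17.
- Read as a between-group main effect, f=0.17 would need 166 (three times) to 194 (two times). The stated 78 therefore does not fit that reading.

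**Step 2: f=0.17 in SD units.** Let δ be the difference between therapies in change from baseline, in units of the SD at a single assessment.
- Two times: each cell's interaction deviation is ±δ/4, so δ = 4f = 0.68 SD.
- Three times, difference sustained after baseline: the half-differences (0, δ/2, δ/2), centred, are (−δ/3, δ/6, δ/6). Their mean square is δ²/18, so δ = f√18 = 0.17×4.243 = 0.72 SD.

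**Step 3: detectable difference at 39 per therapy, 80% power.**

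| Model | ρ | f | δ |
|---|---|---|---|
| Three times, sustained | 0.40 | 0.159 | 0.67 SD |
| Three times, growing linearly (δ at follow-up = f√24) | 0.40 | 0.159 | 0.78 SD |
| Two times | 0.40 | 0.176 | 0.70 SD |
| Three times, sustained | 0.70 | 0.112 | 0.48 SD |

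At 37 per therapy, the sustained three-time figure at ρ=0.40 is 0.69 SD.

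**Step 4: power for smaller true differences** (three times, sustained, ρ=0.40, 39 per therapy). For 0.20 SD: f = 0.20/4.243 = 0.047, power 12%. For 0.37 SD: f = 0.37/4.243 = 0.087, power 31%. For 0.50 SD: power 53%. The 0.20 is this review's reference value for a small difference. The 0.37 is the effect that the article's Table 1 calls small, in its entry for the Finnish trial of KIDNET against treatment as usual; it is a within-group effect and so only a rough guide.

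**Step 5: what a null result would leave open.** For a single change score, the SD of change is √(2(1−0.40)) = 1.095. The 95% half-width is about 1.96×1.095×√(2/39) = 0.49 SD. An observed difference of zero would therefore still be compatible with an advantage of nearly half an SD either way. The change score is used here only for illustration; the plan names the three-time ANOVA.

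**The case against.** The strongest reply is that the article defines its terms. It prints f=0.17 beside the word small, the sample size suffices for that f under the planned analysis, and the size is described only as preferable. All of this stands as far as the number goes.

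A reader might go further and infer that 78 is miscalculated, because f=0.17 needs 84 with two time points, where 78 gives 77% power, or 70 with three. The document does not support that. Two time points are not planned for this comparison, and neither the correlation nor a sphericity correction is given for this calculation. Modest choices return exactly 78, for example three times with a nonsphericity correction of 0.85, or two times with ρ=0.45.

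A reader might also infer that the investigators intend to report non-significance as equality. The article never says so. Research question 3 asks whether a difference exists, which a two-sided difference test does address, and the text commits to CONSORT reporting. What remains is narrower: the stated hypothesis of equal efficacy has no procedure that could confirm it.

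Finally, the SD figures depend on ρ. That is true, but a correlation of 0.70 still leaves about 0.48 SD. A baseline-adjusted analysis, which the article does not plan, would do somewhat better: 0.59 SD for one endpoint, or 0.47 SD for the mean of both post-treatment assessments, at ρ=0.40. Neither is a small difference.

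**Conclusion.** The concern holds as a fault in the claim and in the hypothesis, not in the sample size. The effect that the article calls small is about 0.7 SD in its own planned analysis, and it lies barely below the f=0.20 that the same section calls modest. The trial has roughly a one-in-eight chance of detecting a 0.20 SD difference between the therapies and about a one-in-three chance for 0.37 SD. The equal-efficacy hypothesis rests on a difference test without a margin, which cannot confirm it at any sample size; at this one, a null result would be wide open.

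The figures assume ρ=0.40 carried over from the waitlist calculation, sphericity, 39 analysed per therapy and a difference sustained after baseline. The waitlist comparisons are not affected by this point.

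**What to change.** In Sample size and Objectives, delete the claim to detect a small difference. In its place, state that 39 per therapy gives 80% power for a difference of about 0.7 SD, and name the assumptions (correlation, time points, number analysed). The 78 and the f=0.17 can stay; only the label *small* goes.

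In Statistical analyses, make the EMDR–KIDNET result an estimate with a 95% confidence interval, and state that a non-significant result will not be interpreted as equal efficacy. Reword hypothesis 3 to match, for instance that both therapies are expected to outperform the waitlist and that the difference between them will be estimated.

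The cost is wording and reporting only: no extra children, assessments or change of design. The stated sensitivity becomes less favourable. According to the article, analysis starts only after the final assessment, so the change can be made before any result is known.
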